### SAEs

SAEs are considered in three categories: SAEs that qualify for the primary outcome, other SAEs that are known complications of cardiac surgery, and SAEs that are not known complications of cardiac surgery. The latter will be subject to expedited reporting to the Lead Coordinating Centre. Expedited reporting will also include all fatal events.

### Governance

UK sites have ethics approval through the UK Integrated Research Application System (222991). Non-UK sites or countries are responsible for following their own local governance processes and obtaining the necessary approvals. The University of Bristol is acting as the sponsor for UK sites and as the central coordinating centre for non-UK sites.

### Statistical analysis

Statistical analysis is the responsibility of the Bristol Trials Centre (BTC). A final statistical analysis plan will be written, consistent with the CONSORT guidelines, including the extension for non-pharmacologic treatment interventions,^
15
^ and signed off before any analysis takes place.

Analyses of all outcomes apart from the primary safety outcome will be conducted according to the intention-to-treat (ITT) principle, with participants analysed according to the groups to which they were randomised. A per-protocol (PP) analysis, only including participants who received the intervention to which they were allocated, will be considered for the primary outcome if there are a considerable number of protocol deviators. The safety population will consist of all participants, where participants will be included according to the intervention they received.

#### Primary outcome analysis

The primary outcome will be assessed using a generalised linear model (GLM) to compare trial arms in terms of the risk ratio of experiencing a qualifying SAE up to 30 days after surgery, adjusting for centre and operative procedure.

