**Figure 1. fig1-0267659120946731:**
[figure not shown]
Trial schema. CABG: coronary artery bypass grafting; AVR: aortic valve replacement; CECC: conventional extracorporeal circulation; MiECC: minimally invasive extracorporeal circulation; SAE: serious adverse event.

The trial has three specific objectives:

To estimate the difference between groups in the proportion of participants experiencing the primary outcome (a composite of serious complications) up to 30 days after randomisation.To compare secondary outcomes between groups: serious adverse events (SAE; events which result in death, are life threatening, require hospitalisation or prolongation of hospitalisation, result in persistent or significant disability or incapacity) not included in the primary outcome, red blood cells (RBC) and other blood products transfused; duration of cardiac ICU and hospital stay following the index admission; resource use, generic health status.To estimate the cost-effectiveness of MiECC compared to CECC.

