### Randomisation

Randomisation is performed using a secure Internet-based randomisation system, (Sealed Envelope) and is stratified by centre and surgical procedure (i.e. CABG, AVR, CABG + AVR). Participants are allocated in a 1:1 ratio to either MiECC or CECC. Randomisation takes place as close to surgery as possible and is performed by an authorised member of the local research team. Information to identify a participant and to confirm eligibility must be entered before a number is assigned (i.e. concealed randomisation).

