### Sample size

The trial is powered for the primary composite outcome. The transfusion indication threshold reduction 2 trial (TITRe2) trial, carried out in 17 UK centres, showed a rate of 15-18% in the post-operative SAEs qualifying for the primary outcome in participants receiving CECC, depending on the type of surgery received (CABG, AVR, CABG + AVR).^
14
^ Pooled estimates from previous meta-analyses of the effects of MiECC versus CECC have reported benefits of MiECC for a range of clinical outcomes: odds ratios for 30-day mortality, 0.58^
6
^ 0.40^
7
^ 0.46;^
9
^ for stroke, 0.25^
6
^ 0.40^
7
^ 0.40;^
9
^ for MI, 0.33,^
7
^ 0.40;^
9
^ for post-operative atrial fibrillation, 0.62;^
9
^ renal dysfunction 0.47.^
9
^ A smaller but still clinically important target relative difference, that is, risk ratio of 0.75, was chosen for the trial. In order to detect a risk ratio of ⩽0.75 with 90% power and 5% significance (two-tailed), 2,504 to 3,258 participants are required, depending on the numbers recruited to different surgical strata. We propose to recruit 3,500 participants to allow for uncertainty in the assumptions underpinning this calculation.

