#### Subgroup analyses

Subgroup analyses will be carried out for the primary outcome to compare the trial arms across each level of the following characteristics:

Age (dichotomised by the median)Sex (male, female)Operation type (CABG, AVR and CABG + AVR)EuroSCORE (dichotomised by the median)Preoperative renal dysfunction (dichotomised by the median)Preoperative Hb (dichotomised by the median)

All subgroup analyses will be interpreted with caution and treated as hypothesis-generating.

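### The primary model adjusts only for the two stratification factors; adding EuroSCORE as a continuous covariate would gain some precision at almost no cost

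*Protocol article*

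**What the plan says.** Under Primary outcome analysis, the protocol article specifies a "generalised linear model (GLM) to compare trial arms in terms of the risk ratio", "adjusting for centre and operative procedure". Under Randomisation, allocation is 1:1 and "stratified by centre and surgical procedure", so the model contains the stratification factors and nothing else.

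The list under Subgroup analyses includes "EuroSCORE (dichotomised by the median", together with age, sex, operation type, preoperative renal dysfunction and preoperative haemoglobin. Table 1 places baseline data collection at the pre-admission clinic or the day before the operation. EuroSCORE is therefore expected to be held as a pre-treatment variable, but it has no role in the main comparison.

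The Sample size section gives the planning values. An earlier UK trial "showed a rate of 15-18% in the post-operative SAEs qualifying for the primary outcome in participants receiving CECC"; a "risk ratio of 0.75, was chosen for the trial"; power is 90% at two-sided 5%; 2,504 to 3,258 participants are required; and the recruitment target is 3,500. The Statistical analysis section says that a final SAP is still to be written and signed off before any analysis.

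**The concern.** The primary outcome combines 12 post-operative complications, among them death, myocardial infarction, stroke and acute kidney injury. A preoperative operative-risk score is a natural candidate predictor of such a composite. In a randomised trial of this size, adjusting for a pre-specified baseline predictor introduces no material bias. It removes outcome variation unrelated to treatment and accounts for chance imbalance in operative risk that stratifying on centre and procedure does not control.

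The covariate set is named in the article and not left open, so the SAP would be expected to carry it forward. What is at stake is precision in the primary comparison that could be had without new patients or new data.

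**Working it through.** **Inputs from the article.** Control risk 15-18%; risk ratio 0.75; two-sided 5%; 1:1 allocation; planned N = 3,500.

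**Input not in the article (assumption).** R², the share of outcome variance that EuroSCORE explains beyond centre and procedure. The article gives no R², AUC or similar figure, so a range of 1-10% is shown.

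**Step 1: the plan's own figure.** The usual two-proportion formula with pooled variance, at 90% power, gives a total of 3,404 for 15% versus 11.25% and 2,750 for 18% versus 13.5%. With continuity correction these become 3,510 and 2,840. Neither pair matches the stated 3,258 and 2,504, which are reproduced with continuity correction at control risks of 16% and 20%. That is a separate question about the sample size. The power figures below use the planned 3,500 and do not depend on it.

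**Step 2: power of the plan as it stands.** With n = 1,750 per arm, p₁ = 0.15, p₂ = 0.1125 and mean 0.13125:

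z = [(p₁ − p₂)√n − 1.96 √(2p̄(1 − p̄))] / √(p₁(1 − p₁) + p₂(1 − p₂))

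= (1.5687 − 1.96 × 0.4775) / 0.4768 = 1.327, so power is 90.8%.

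At 18% control risk the same formula gives 95.5%.

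**Step 3: gain from adjustment.** To a good approximation, adjusting for a baseline covariate with 1:1 allocation multiplies the variance of the marginal estimate by (1 − R²). The trial then behaves like one of size N/(1 − R²), and the gain in participants is N/(1 − R²) − N. Power is recomputed with n/(1 − R²) per arm.

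| Assumed R² | Equivalent extra participants at N = 3,500 | Power, 15% control risk | Power, 18% control risk |
|---|---|---|---|
| 0 (as planned) | 0 | 90.8% | 95.5% |
| 1% | 35 | 91.0% | 95.7% |
| 2% | 71 | 91.3% | 95.9% |
| 5% | 184 | 92.1% | 96.3% |
| 7% | 263 | 92.6% | 96.7% |
| 10% | 389 | 93.4% | 97.1% |

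At 15% control risk the gain is about 0.3 to 2.6 percentage points (unrounded, 90.78% to 91.05% and 93.38%). At 18% it is about 0.2 to 1.6 points.

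**Step 4: what R² of 1-10% means.** With a logistic model, a normally distributed risk score and an event rate of 13% (close to the mean of 13.1% in Step 2), R² of 1.0% corresponds to an AUC of about 0.58, 4.1% to 0.66, 7.1% to 0.71 and 10.7% to 0.75. These R² values are against a model with no covariates. Centre and procedure already account for some of the risk, so the increment that matters may be smaller than a given AUC suggests.

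**Step 5: if recruitment falls short.** The article reports 603 randomised by 11 May 2020 at 40-50 a month, with recruitment scheduled for three years from September 2020. If that rate simply continued for about 39.5 months (an assumption; the sponsor aims to raise it), the total would be 603 + 39.5 × 40 ≈ 2,180 to 603 + 39.5 × 50 ≈ 2,580. At N = 2,400 and 15% control risk, power is 77.7% without EuroSCORE and 78.1-81.8% with R² of 1-10%, a gain of 0.4 to 4.1 points.

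**The case against.** The strongest reply is that nothing is wrong. Adjusting for the stratification factors matches the design and gives a valid analysis. The target of 3,500 was set above the calculated range to absorb uncertainty, and it already gives at least 90% power across 15-18%. The SAP is not yet written and could add covariates. All of this stands, and it limits the point to a modest improvement. It does not remove the point, because the article names a covariate set and a better one is available from a variable it already plans to use.

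The reply is also right that the article does not show EuroSCORE to be a strong predictor here. The composite is varied and includes reoperation, percutaneous intervention, sternal wound dehiscence and septicaemia.

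Stronger readings are tempting but unsupported:

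- A reader might infer a definite number of patients lost, for example 130-260. At N = 3,500 that band needs R² of about 3.6-6.9%, which no figure in the article establishes.
- A reader might infer that the trial lacks power without this change, since 3,258 participants at 15% control risk give only 88.7%. The planned number is 3,500, and any shortfall at 3,258 is a sample-size matter.
- A reader might infer that every subgroup variable is recorded for every participant. The article lists the variables but says nothing about completeness.
- The first objective is "To estimate the difference between groups in the proportion of participants experiencing the primary outcome", whereas the model targets a risk ratio. That difference in wording is a separate matter and lends no weight to this point.

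**Conclusion.** The point holds as a missed efficiency. The primary model is valid but omits a patient-level risk score that the trial expects to hold. Under the assumed R² of 1-10% beyond centre and procedure, the gain is worth about 35-390 participants at N = 3,500, or about 0.3 to 2.6 power points at 15% control risk, and somewhat more if fewer are recruited. Because centre and procedure already explain part of the risk, the lower part of that range is quite possible. The direction of the gain is well founded if EuroSCORE is prognostic for the composite; its size cannot be fixed from the article.

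**What to change.** In the primary outcome analysis, and in the SAP before any outcome data are examined by arm, pre-specify EuroSCORE as a continuous covariate (not split at the median) alongside centre and operative procedure. Report the marginal risk ratio by standardisation over the trial population, with a robust standard error. Keep the centre-and-procedure model as a sensitivity analysis. Name EuroSCORE alone as the added covariate, so that the set is closed in advance.

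The cost is small: a short addition to the text, a simple stated rule for missing baseline scores, and slightly more analysis work for the standardisation and the sensitivity analysis. No additional patients are needed and, as EuroSCORE is already a planned subgroup variable, no additional data collection.

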#### Secondary outcome analyses

Binary secondary outcomes (all-cause mortality at 30 days after surgery; any other SAE at 30 days after surgery; any RBC transfusion; any platelet transfusion; any fresh frozen plasma transfusion) will be assessed separately, using GLMs as for the primary outcome. The total number of units of blood products transfused will also be analysed using linear regression, adjusting for centre and operative procedure, for all blood products.

Time to death, time to discharge from CICU and time to discharge from hospital will be assessed using Cox proportional hazards models to compare the trial arms, adjusting for centre and operative procedure, for both analyses. Median survival with 95% confidence intervals will be estimated by trial arm and overall for both analyses.

Generic health status (EQ-5D-5L) will be analysed using a linear mixed effects model. Mean QoL scores and 95% CIs will be summarised at baseline, 30 days and 90 days.

Occurrence and frequency of all safety events (SAEs that do not qualify for the primary outcome) will be summarised by trial arm and overall.

#### Subgroup analyses

Subgroup analyses will be carried out for the primary outcome to compare the trial arms across each level of the following characteristics:

Age (dichotomised by the median)Sex (male, female)Operation type (CABG, AVR and CABG + AVR)EuroSCORE (dichotomised by the median)Preoperative renal dysfunction (dichotomised by the median)Preoperative Hb (dichotomised by the median)

All subgroup analyses will be interpreted with caution and treated as hypothesis-generating.

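### Four continuous effect modifiers are fixed as sample-median splits, which loses about 36% of the interaction information if the covariate is normal and the modification linear

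*Protocol article*

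**What the plan says.** The Subgroup analyses section of the protocol article sets out the approach in one sentence: "Subgroup analyses will be carried out for the primary outcome to compare the trial arms across each level of the following characteristics". Six characteristics follow. Sex and operation type are categorical. The other four are continuous or near-continuous measures, and each has its cut fixed (quoted here without the closing bracket): "Age (dichotomised by the median", "EuroSCORE (dichotomised by the median", "Preoperative renal dysfunction (dichotomised by the median" and "Preoperative Hb (dichotomised by the median".

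The section closes with a caveat: "All subgroup analyses will be interpreted with caution and treated as hypothesis-generating".

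Two other places matter. Primary outcome analysis specifies a "generalised linear model (GLM) to compare trial arms in terms of the risk ratio of experiencing a qualifying SAE", adjusted for centre and operative procedure. Statistical analysis defers detail: "A final statistical analysis plan will be written, consistent with the CONSORT guidelines". That plan is not available here.

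**The concern.** The subgroup question is whether the effect of MiECC on the composite outcome changes with age, operative risk, renal function or haemoglobin. A median split answers it inefficiently. Everyone on one side of the cut is treated as alike, and two patients just either side of it are treated as different.

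The cut also has no fixed meaning. It will be whatever the middle of the recruited sample turns out to be, pooled over centres in several countries, so it cannot be stated in advance or carried to another population. The renal factor shows this best: it is named as dysfunction, yet by construction half of participants land on the less favourable side, however good or poor renal function in the sample is.

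At stake is the precision and readability of the effect-modification results. The primary comparison does not depend on them.

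**Working it through.** **Inputs.** From the article: planned N = 3,500, 1:1 allocation, control event rate 15–18% (Sample size, Randomisation); four median splits (Subgroup analyses). The article gives no figure for subgroup precision, so there is none to reproduce, and it reports no covariate distributions. Distributions and interaction sizes below are therefore assumptions.

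**Information kept by a median split.** Treatment is randomised and so independent of the covariate X. To a good approximation, the efficiency of testing a linear interaction with the split variable D in place of X is the squared correlation of X and D. With D = ±1 either side of the median m, each with probability one half,

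corr(X, D) = E|X − m| / SD(X), and information kept = [E|X − m| / SD(X)]².

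- Normal: E|X − m|/SD = √(2/π) = 0.798. Kept 0.637, lost 36%. The standard error on a common scale is 1/0.798 = 1.25 times larger. Equivalent sample: 0.6366 × 3,500 ≈ 2,228.
- Uniform on (−1, 1): 0.5 / (1/√3) = 0.866. Kept 0.75, lost 25%.
- Exponential: ln 2 / 1 = 0.693. Kept 0.48, lost 52%.
- By simulation with 2,000,000 draws: t with 5 df lost 46%; lognormal (σ = 0.5) lost 48%; lognormal (σ = 1) lost 73%.

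The larger losses for skewed shapes assume the interaction is linear on the raw scale. If it is linear on the log scale, a lognormal covariate returns to the 36% figure, because a median split is unchanged by a monotone transformation.

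**Power of the interaction test at N = 3,500.** Trials were simulated with a standard normal covariate and a logistic model. The interaction was tested at two-sided 5%, once with X continuous and once with X split at its median.

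- Setting A: control rate 16.5% at the covariate mean, covariate log-OR 0.3 per SD, treatment log-OR ln 0.72 = −0.33, 800 runs.
- Setting B: overall control rate 15%, covariate log-OR 0.5 per SD, treatment log-OR −0.33, 1,500 runs.

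| Setting | Interaction log-OR per SD | Continuous | Split | Gap (points) |
|---|---|---|---|---|
| A | 0.20 | 54% | 38% | 16 |
| A | 0.30 | 87% | 67% | 20 |
| B | 0.20 | 46% | 33% | 13 |
| B | 0.25 | 65% | 45% | 20 |
| B | 0.30 | 80% | 59% | 21 |

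The simulation standard error is at most √(0.25/800) = 1.8 points in A and √(0.25/1,500) = 1.3 points in B.

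**Cross-check.** Power of 54% means an expected z of about 1.96 + 0.10 = 2.06. Multiplied by 0.798 this is 1.64, and Φ(1.64 − 1.96) = Φ(−0.32) = 37%, against 38% simulated. The formula and the simulation agree.

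**Where the loss arises.** Both columns test an interaction. The gap therefore comes from dichotomising alone: an interaction term built on the split variable loses the same 36%.

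**The case against.** The strongest reply is that these analyses are explicitly exploratory and that none of the three stated objectives concerns subgroups. A median rule named in advance also cannot be tuned to the outcome data, gives balanced groups and makes a simple forest plot. All of that stands, and it is why the point is minor. It does not recover the lost information or give the cut a meaning.

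The magnitude is also conditional.

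- The simulated interactions are large. With treatment log-OR −0.33, an interaction of 0.30 per SD means an OR of exp(−0.63) = 0.53 at −1 SD and exp(−0.03) = 0.97 at +1 SD.
- The simulations use odds ratios, while the plan's model uses the risk ratio. Interaction depends on scale, so the powers are indicative only.
- If the modification were a step exactly at the median, the comparison would reverse: by the same squared correlation, the linear term would keep 64%. A threshold elsewhere narrows or removes the advantage of the linear term.

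A reader might infer something stronger: that the arms will be compared separately in each half with no interaction test, inviting a reading that one half benefits and the other does not. The article does not support that as a criticism. Its wording neither names nor excludes an interaction term and is compatible with subgroup risk ratios plus an interaction test from the primary model. A condensed article commonly leaves that detail to the analysis plan.

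A reader might also infer that a single Hb median mainly separates men from women. The article gives neither the sex mix nor any Hb values, so that point is not made.

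**Conclusion.** The point holds as a minor improvement. The median splits of the four continuous factors are fixed in the text, so this concerns a stated choice and not an omitted detail.

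Under a roughly normal covariate and linear modification, the split discards about 36% of the interaction information. The range is 25% for a uniform covariate to about half or more for skewed ones, on assumed shapes. In the simulated scenarios at N = 3,500 this costs 13 to 21 points of power. Separately, and without any distributional assumption, the cut is defined by the recruited sample, so the renal factor does not identify patients with renal dysfunction.

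The primary comparison, its power and its error rate are untouched.

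**What to change.** For age, EuroSCORE, preoperative renal function and preoperative Hb, state that the subgroup result is the treatment-by-continuous-covariate interaction, fitted in the risk-ratio GLM already specified for the primary outcome. Report the interaction estimate with its 95% CI, and check for non-linearity, for example with a spline. Show the risk ratio at covariate values set in the analysis plan, so that they do not move with the sample. Keep the median-split rows in the forest plot for display only. Sex and operation type stay as they are, and so does the exploratory label.

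The cost is a few lines of wording and slightly more programming, with no new data, since the subgroup analyses already need these measures. There are three downsides. The forest plot is less simple. The gain shrinks, and may reverse, if modification is a threshold and not a gradient. A log-link binomial fit can also fail to converge once a continuous covariate enters, so the analysis plan should name a fallback such as Poisson regression with robust standard errors.

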#### Cost-effectiveness analysis

The cost-effectiveness of MiECC compared to CECC will be estimated for COMICS participants recruited in England (approximately 600 participants), using quality-adjusted life years as the outcome measure estimated using the EQ-5D-5L, which can be mapped on to ‘valuations’.^
16
^

Costs of resource use for English participants will be estimated using linked Hospital Episode Statistics (HES) data and information from a previous trial.^
13
^ We will calculate average costs and outcomes associated with MiECC and CECC and produce an incremental cost per quality adjusted life year (QALY) gained with MiECC compared to CECC. If there are differences in mortality between trial arms, then costs and outcomes will be extrapolated to a longer time horizon. Scenario analyses will use EQ-5D-5L data from all participants and cost data from English participants.

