### Trial outcomes

#### Primary outcome

The primary outcome is a composite of post-operative SAEs occurring up to 30 days after randomisation following the index admission. All SAEs that qualify for the primary outcome are objectively defined or will be adjudicated. The following events qualify:

(a) All-cause mortality up to 30 days after surgery(b) Myocardial infarction (MI)(c) Permanent stroke(d) Gut infarction(e) AKI (Acute kidney injury–an acute increase in serum creatinine > 26.4 μmol/L or a percentage increase in serum creatinine of more than or equal to 50%) Network criteria for stage 3 AKI^
11
^(f) Reintubation(g) Tracheostomy(h) Mechanical ventilation for >48 hours, including multiple episodes when separated by more than 12 hours(i) Reoperation(j) Percutaneous intervention(k) Sternal wound infection with dehiscence(l) Septicaemia confirmed by microbiology

Events will be documented as follows: suspected MI by serum troponin concentrations and electrocardiograph recording (ECG); stroke from brain imaging (CT or MRI) report and record of new onset focal or generalised neurological deficit; gut infraction by laparotomy or post-mortem; other events from the medical record. Equivocal events will be adjudicated.

Secondary outcomes are as follows:

(a) All-cause mortality up to 30 days after surgery(b) Other SAEs up to 30 days after surgery (primary safety outcome)(c) Units of RBC transfused up to 30 days after surgery(d) Other blood products transfused up to 30 days after surgery(e) Time to discharge from cardiac ICU during the index admission(f) Time to discharge from hospital following the index admission(g) Delirium in ICU, assessed with the Intensive Care Delirium Screening Checklist (ICDSC)^
12
^ for up to 5 days (only collected at some centres).(h) Generic health status using the EuroQol 5-level health status questionnaire (EQ-5D-5L)^
13
^ at 30 and 90 days after randomisation(i) Health resources and associated costs up to 90 days after randomisation (UK centres only)

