### Data collection

Participants are followed up twice, at 30 days and 90 days after surgery. Questions elicit information about SAEs (including readmissions) experienced since discharge up to 30 days after the date of surgery. Generic health status is assessed around both 30 and 90 days. The schedule of data collection is outlined in Table 1. Data are collected from participants or their medical records, entered into a bespoke database and stored on a secure server.

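### Extrapolation beyond the 90-day follow-up is made conditional on the observed mortality result; both horizons should be reported whatever mortality shows

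*Protocol article*

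**What the plan says.** The Cost-effectiveness analysis section estimates cost-effectiveness for "COMICS participants recruited in England (approximately 600 participants". It commits, without condition, to "produce an incremental cost per quality adjusted life year (QALY) gained with MiECC compared to CECC". The next sentence adds the rule at issue: "If there are differences in mortality between trial arms, then costs and outcomes will be extrapolated to a longer time horizon". The section closes with "Scenario analyses will use EQ-5D-5L data from all participants and cost data from English participants".

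The follow-up that feeds this analysis is short. The outcome list has "Health resources and associated costs up to 90 days after randomisation (UK centres only", and the Data collection section says "Generic health status is assessed around both 30 and 90 days". On mortality, the listed secondary outcome is "All-cause mortality up to 30 days after surgery". The Secondary outcome analyses section also plans a Cox model for time to death. Nothing else in the article changes the rule or promises a long-horizon analysis in every case.

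**The concern.** The time horizon is a structural choice in an economic evaluation. Here, whether a horizon beyond the trial is used at all depends on the mortality data that the analysis is meant to value. Without extrapolation, one participant can accrue at most about 90/365 = 0.25 QALY, so an averted death counts for very little. With extrapolation, it can dominate the QALY difference.

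A health economics plan could define what a difference is and in whom it is judged, and leaving that detail to such a plan would be unremarkable. But any threshold set there would still make the long-horizon analysis depend on the result. The condition itself is stated in this text, and it is the condition that is the problem. Cost-effectiveness is one of the trial's three specific objectives. The Discussion also notes that the higher consumable costs of MiECC may be offset by clinical benefits, so the treatment of survival bears directly on the economic conclusion.

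**Working it through.** The article gives no figure for how the rule behaves, so there is none to reproduce.

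**Inputs from the article.** About 600 English participants, randomised 1:1, so 300 per arm; 3,500 planned in total, so 1,750 per arm; odds ratios for 30-day mortality of 0.58, 0.40 and 0.46 (Sample size section).

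**Assumption.** The article calls mortality low but gives no rate. I take control mortality p as 1.5%, 2% and 3%.

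**Reading 1: a significant difference is required (two-sided 5%).** MiECC mortality is q = o/(1 + o), with o = OR × p/(1 − p). For 300 per arm, I summed the binomial probabilities of all pairs of death counts that are significant by Fisher's exact test. For 1,750 per arm, I used the normal approximation: power = Φ{[(p − q)√n − 1.96√(2m(1 − m))] / √(p(1 − p) + q(1 − q))}, with m = (p + q)/2.

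Worked example with p = 2%, OR 0.58, n = 1,750:
- o = 0.58 × 0.02/0.98 = 0.01184, so q = 0.01170 and p − q = 0.0083.
- Numerator: 0.0083 × 41.83 − 1.96 × 0.1766 = 0.347 − 0.346 = 0.001.
- Denominator: 0.1765, so power = Φ(0.006) = 0.50.

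| Control mortality | OR | MiECC mortality | True difference (points) | 300 per arm, exact | 300 per arm, normal approx. | 1,750 per arm, normal approx. |
|---|---|---|---|---|---|---|
| 1.5% | 0.58 | 0.88% | 0.62 | 4% | 10% | 40% |
| 1.5% | 0.40 | 0.61% | 0.89 | 8% | 19% | 74% |
| 2% | 0.58 | 1.17% | 0.83 | 6% | 13% | 50% |
| 2% | 0.40 | 0.81% | 1.19 | 13% | 24% | 85% |
| 3% | 0.58 | 1.76% | 1.24 | 11% | 17% | 67% |
| 3% | 0.40 | 1.22% | 1.78 | 23% | 33% | 96% |

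The odds ratio 0.46 lies between these rows.

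**Selection under reading 1.** With 300 per arm, the smallest gap that reaches significance is 6 deaths against 0. Its two-sided p is 2 × (300·299·298·297·296·295)/(600·599·598·597·596·595) = 0.030, while 5 against 0 gives 0.061. So every extrapolated difference would be at least 6/300 = 2.0 points, which is more than any true difference in the table (0.62-1.78). With 1,750 per arm the selection is milder. In the worked example the threshold is 0.346/41.83 = 0.83 points, which is the true difference itself, so only estimates at or above the truth would be carried forward.

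**Reading 2: any numerical difference suffices.** With equal true mortality, P(death counts differ) = 1 − Σ b(k; n, p)², where b is the binomial probability of k deaths. For p = 1.5%, 2% and 3%:
- 300 per arm: 86%, 88%, 90%.
- 1,750 per arm: 94%, 95%, 96%.

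**What the horizon is worth.** This is an illustration, assuming utility 0.8, 3.5% discounting and a 10-year horizon. One death fewer per 300 gives (1/300) × 0.8 × (1 − 1.035^−H)/ln 1.035 QALY per patient.
- H = 0.25 years: 0.8 × 0.249/300 = 0.0007.
- H = 10 years: 0.8 × 8.46/300 = 0.023.

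The ratio is about 34.

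**Precision of the mortality difference.** SE = √(2p(1 − p)/n). For p = 1.5-3% this is 0.99-1.39 points with 300 per arm and 0.41-0.58 points with 1,750 per arm.

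**The case against.** Several stronger readings are tempting, and the article does not support them.

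- *Chance among 600 participants decides the horizon.* The rule refers to trial arms without restriction, and the primary, secondary and subgroup analysis sections use that term for whole-trial comparisons. Where the section means the English subset, it says so. A whole-trial mortality comparison is at least as natural. It matters: with no true difference and 1.5-3% mortality, a chance gap of at least 1 point occurs in 39-55% of trials with 300 per arm but only 2-8% with 1,750 per arm.
- *A numerical trigger biases the result.* It hardly can. It is nearly the same as always extrapolating, and when deaths are equal, extrapolation adds essentially no mortality-driven difference. With no true effect, the projected difference averages zero. The result is imprecise, not biased, and an unconditional long-horizon analysis would also project chance differences. Only pooling deaths across the trial shrinks them.
- *The long horizon replaces the 90-day result.* Nothing says so. The cost per QALY is promised first and without condition, and extrapolation is added to it.
- *The analysis wastes most of the data.* English participants are 600/3,500 = 17% of the total, but the restriction follows from costing through linked hospital records. EQ-5D-5L data from all participants enter the scenario analyses.

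These objections limit the point, and I accept them. They do not justify the condition. Under reading 1 it suppresses a needed analysis, and under reading 2 it does almost nothing.

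**Conclusion.** The rule is a poor one as stated. If significance is required, a true mortality benefit of the size the article cites would lead to a long-horizon analysis in about 4-23% of trials when judged in 600 participants, or 40-96% when judged in 3,500. In the remaining trials the benefit gets no value beyond about 90 days, and where extrapolation is done, the difference carried forward is selected for being large. If any numerical difference is enough, the condition is redundant.

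These sizes rest on the assumed control mortality of 1.5-3%, and the 34-fold QALY contrast also rests on the assumed utility, discount rate and horizon. The two ranges use different methods; the table gives both for 300 per arm. The article leaves open which reading and which population apply, so it would be wrong to conclude that the cost per QALY will be decided by chance or is biased on every reading. The point concerns the economic objective only. It is a cheap improvement and leaves the primary outcome analysis untouched.

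**What to change.** 1. Delete the condition. State that a long-horizon analysis will be reported alongside the already planned 90-day analysis, whatever the mortality comparison shows.
2. Take the mortality effect and its uncertainty from all randomised participants, and carry that uncertainty through the model probabilistically. This cuts the SE of the mortality difference from about 1.0-1.4 points to about 0.4-0.6 points. Keep unit costs and resource use from the English participants.
3. Name the mortality measure and the population used for the extrapolation.

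The cost is wording in the protocol or health economics plan, with no new data collection. The downside is that the long-horizon model, which the article foresees only conditionally, must be built in every case.
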